### Analysis of the oral health impact profile (OHIP-14 questionnaire)

3.11

The oral health impact profile (OHIP-14) is a simplified form of the original OHIP questionnaire that is used to assess the impact of oral health on subjects’ quality of life. The items are distributed among the following subscales: functional limitation, pain, psychological discomfort, physical disability, psychological deficiency, social incapacity and disability. The questionnaire will be applied by the evaluator in the preoperative period and 7 days after surgery.

### Anxiety analysis

3.12

The analysis of anxiety will be done through Beck's inventory of anxiety that evaluates, by quantitative approximation, anxiety symptoms. The questionnaire contains 21 aspects that reflect somatically, cognitively and affectively the characteristic symptoms of anxiety. The questionnaire also presents high reliability, high internal consistency and moderate validity, both for psychiatric participants and for general population samples.^[20]^ The inventory consists of 21 items that are descriptive statements of the symptoms common in anxiety pictures and that should be evaluated by the individual with reference to himself in the period of one week in a scale of 4 points that reflect levels of increasing severity of each symptom, whose alternatives are: absolutely not; lightly: It did not bother me much; moderately: It was very unpleasant, but I could bear it; seriously: I could hardly bear it. At the end, the items are summed and the total score can vary from 0 to 63. All participants will respond to this questionnaire in the preoperative period and at 7 days postoperatively.

### Statistical analysis

3.13

Initial descriptive analyses will be performed considering all variables measured in the study, both quantitative (mean and standard deviation) and qualitative (frequencies and percentages). Later, the appropriate statistical tests will be applied for each specific analysis. In all tests, the significance level of 5% probability or the corresponding p-value will be adopted. All analyses will be performed using the statistical software SAS for Windows, version 9.1.3.

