## Introduction

1

Photobiomodulation (PBM) is an emerging technique using red or near infrared light (low-power laser or light emitting diode [LED]) to modulate inflammation, accelerate wound healing, and reduce pain and discomfort in different clinical situations.^[1,2]^ The efficacy of PBM depends on the parameters, such as wavelength, power output, and energy. Different clinical situations require different PBM protocols. Most of the research on PBM in dentistry was carried out with low power/intensity lasers and some protocols are already well established using these lasers.^[2]^ However, few studies in dentistry were developed using LEDs, and most of them were performed to prevent/treat oral mucositis.^[3]^

Some studies have demonstrated a beneficial effect of LED (670 nm) on the incidence and severity of oral mucositis in participants undergoing oncological treatment.^[4–6]^ However, the near-infrared light in the 850 nm range has been shown to be capable of promoting vasodilation and the production of growth factors, as well as angiogenesis, leading to wound healing.^[7,8]^

In dentistry, one of the most common surgical procedures is the removal of retained third molars.^[2,9]^ This surgery generates great morbidity to the participants by causing pain, edema, and trismus due to surgical trauma.^[2,10,11]^ In recent years, several studies have shown beneficial effects of low intensity laser therapy in the postoperative period of lower third molar extractions.^[12–14]^. Despite the beneficial effects of LEDs on pain control and repair described in the literature, no studies were found to evaluate the effect of the use of LEDs in the postoperative period of third molar surgery. This is a relatively new technology and it is still under investigation especially in clinical trials.

The objective of the present study is to evaluate the efficacy of LED photobiomodulation in pain control, facial edema, trismus, temperature, dysphagia, hematomas, and quality of life after the extraction of retained lower third molars.

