### Sample calculation

2.3

A sample calculation based on the parameters of variability of the article of Eshghpour, Ahrari ^[13]^ based on the pain analysis of the participants on the 3rd postoperative day evaluated by a visual analog scale (VAS) was performed. Using a power of 80% and level of significance of 5%, a minimum sample size of 17 cases per group was obtained, making a total of 34 participants for the study. Winpepi software version 10.5 was used for this calculation. Considering a loss of 10%, based on the study that was used for the sample calculation, a loss of 2 participants per group should be predicted. Therefore, the total number of participants to be selected will be 38 individuals.

*Inclusion criteria*:Need of surgical removal of retained lower third molars;Agree to participate in the study after reading and signing the Informed Consent Term;Participants with indication for extraction of lower third molars (recurrent infections, bad position, and orthodontic indication) or professional written indication, healthy patients (negative medical history), systolic blood pressure lower than 140 mm Hg, and diastolic blood pressure lower than 90 mm Hg and heart rate values of 70 ± 20 beats/minute. The upper and lower central incisor teeth must be present.

*Exclusion criteria*:Systemic diseases, chronic pain or neurological and psychiatric disorders;Smokers;Using anti-inflammatories, analgesics or bisphosphonates in the last 15 days;Present active pericoronarite;Pregnant;Breastfeeding;Severe temporomandibular disorders;Photosensitivity history;Allergic to any drug used in the research (paracetamol, chlorhexidine 2%);Participants presenting radiolucent images associated with the teeth to be extracted;Participants who present any type of complication during surgery (hemorrhage, operative difficulty, time greater than 90 minutes of surgery), as these cases are not in the standard expected for third molar surgeries. In this case, the central action analgesic will be prescribed. These data will not be part of the statistical analysis but will be described and discussed.

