### Postoperative pain evaluation

3.5

In this project, we intend to apply 2 scales: the VAS and NRS-101. The VAS will be printed on the patient evaluation form and the subjects will be instructed by the evaluator to mark a point on the 10 cm line, indicating the intensity of their pain after 1.2, 5, and 7 days of the surgeries For the NRS-101 scale, the evaluators will ask participants to assign a number between 0 (no pain) and 100 (worst possible pain) that best represents the pain they are currently experiencing after 1, 2, 5, and 7 days of surgeries.

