### Evaluation of postoperative edema

3.6

The evaluator will measure the distances between the corner of the eye and angle of the mandible, between tragus and labial commissure, and between tragus and pogonium^[14]^ of each patient 1, 2, 5, and 7 days after surgery.

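### Every test is set at 5%, no outcome and day is identified as deciding efficacy, and the outcome used for sizing falls on a day the trial does not assess

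*Protocol article*

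**What the plan says.** The Introduction states the objective as "to evaluate the efficacy of LED photobiomodulation in pain control, facial edema, trismus, temperature, dysphagia, hematomas, and quality of life". These seven targets stand side by side, and no section of the article calls any of them primary.

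Section 3.5 adds a second pain measure: "In this project, we intend to apply 2 scales: the VAS and NRS-101". It does not say which scale decides. Section 3.6 measures edema as three separate facial distances: "The evaluator will measure the distances between the corner of the eye and angle of the mandible, between tragus and labial commissure", with tragus to pogonium as the third. The Abstract and section 3.4 put the postoperative assessments on days 1, 2, 5 and 7.

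Section 2.3 describes the sample size as "based on the pain analysis of the participants on the 3rd postoperative day evaluated by a visual analog scale (VAS) was performed" and continues: "Using a power of 80% and level of significance of 5%, a minimum sample size of 17 cases per group was obtained".

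Section 3.13 leaves the tests open, "Later, the appropriate statistical tests will be applied for each specific analysis", but fixes the level: "In all tests, the significance level of 5% probability or the corresponding p-value will be adopted".

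**The concern.** A 5% level protects a trial's conclusion only if it is known in advance which result carries that conclusion. Here the level applies to each test separately, and the article offers many candidate results without ranking them.

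A reader would normally look to the sample size for the implied primary outcome. That fails here, because day 3 is not an assessment day. VAS on day 3 will not exist in the data, and the article does not say which assessed day takes its place.

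The article describes the trial as the first of LED in this setting. If one facial distance on one day, or one pain scale on one day, reaches p<0.05, nothing in the article tells a reader whether that result was meant to decide or was one of many. The error rate behind such a result could be several times the nominal one.

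**Working it through.** **The plan's own figure.** The 17 per group cannot be rebuilt, because the article gives neither a difference nor an SD; it refers to a cited study ("A sample calculation based on the parameters of variability of the article"). Working backwards from 17 per group, 80% power and two-sided 5% (sidedness is my assumption), the implied standardised difference is (1.960 + 0.842) × √(2/17) = 0.96 by the normal formula, or 0.99 by the t distribution. The allowance for loss does reproduce: 17/0.90 = 18.9, rounded up to 19 per group, 38 in total.

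**Day used for sizing against days assessed.** Section 2.3 uses day 3. The Abstract and sections 3.4 and 3.5 give days 1, 2, 5 and 7. There is no overlap.

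**Counting comparisons.** The article does not fix the number of tests. One between-group test per measure per assessed day would give:

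| Measure (section) | Tests |
|---|---|
| VAS and NRS-101 (3.5) | 2 × 4 = 8 |
| Facial distances (3.6) | 3 × 4 = 12 |
| Mouth opening (3.7) | 4 |
| Temperature: operated side, opposite side, systemic (3.8) | 3 × 4 = 12 |
| Dysphagia (3.9) | 4 |
| Hematoma (3.10) | 4 |
| OHIP-14, day 7 (3.11) | 1 |
| BAI, day 7 (3.12) | 1 |
| Total | 46 |

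One repeated-measures analysis per measure would give 11 + 2 = 13 tests.

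**Chance of at least one p<0.05 under no effect, independent tests.** The formula is 1 − 0.95^k. For results favouring LED only it is 1 − 0.975^k.

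| Set of tests | k | Either direction | Favouring LED |
|---|---|---|---|
| VAS on four days | 4 | 18.5% | 9.6% |
| Both pain scales on four days | 8 | 33.7% | – |
| 13 outcomes, one test each | 13 | 48.7% | 28.0% |
| All outcome-by-day tests | 46 | 90.6% | 69% |

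**Allowing for correlation.** Measures in the same patients are correlated, but the article gives no correlations, so these are assumed. Simulation of 46 correlated normal test statistics (40,000 runs, no true effect) gives:

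| Correlation between outcomes / between days | Either direction | Favouring LED |
|---|---|---|
| 0.3 / 0.5 | 80% | 47% |
| 0.5 / 0.5 | 71% | 39% |
| 0.7 / 0.7 | 49% | 25% |
| 0.8 / 0.9 | 31% | 16% |

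For the eight pain tests alone, a common correlation of 0.5 to 0.8 lowers 34% to between 25% and 16%. The nominal rates are 5% in either direction and 2.5% favouring LED. Every scenario in the two tables exceeds them.

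The expected number of nominally significant results among 46 tests is 46 × 0.05 = 2.3, whatever the correlation.

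**The case against.** Several points on the other side stand.

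- **No success rule is stated.** A reader might infer that any single result below 0.05 would count as proof of efficacy. Section 3.13 does not say so. It sets a level per test and claims no trial-wide error rate. The defect is that nothing says which result decides.
- **A false efficacy claim is not shown to be likely.** A reader might take the 91% as the chance of a false claim for LED. It assumes independence and counts results against LED. Counting only results in favour, every correlated scenario tabulated above is below one half.
- **The small sample is not the cause.** A reader might blame the 38 participants for chance findings. A valid 5% test has a 5% error rate under no effect at any sample size.
- **The 46 tests are an assumption.** Repeated-measures models would cut them to about 13, and the unoperated-side temperature may only be a reference. Dropping it leaves 42 tests and 88% if independent.
- **Pain has some priority.** The title and the Abstract's objective name only pain, edema, trismus and quality of life, with pain first, and pain on the VAS is the sizing variable. Leaving out temperature, dysphagia, hematoma and BAI removes 12 + 4 + 4 + 1 = 21 tests. The remaining 25 still give 1 − 0.95^25 = 72% if independent. Even if VAS pain is taken as the lead outcome, four days remain and the sizing day is none of them.
- **Other documents are not shown.** The registry record, SPIRIT checklist, SPIRIT figure or an analysis plan may name a primary outcome. A multiplicity method can also be left to an analysis plan, and its absence is not the point here. The point is what the article does fix: a uniform 5%, unranked efficacy outcomes, and a sizing variable that is not collected.

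**Conclusion.** The point holds. On the article as written, no outcome and time is identified as deciding efficacy, and the sample size cannot supply one because it refers to a day without an assessment. The false-positive rate across the planned outcomes is therefore well above 5%. How far above depends on a test count and correlations that the article does not give: 18.5% for VAS alone on four days if independent, 49% for 13 outcomes tested once if independent, and about 31% to 91% for 46 tests in either direction (about 16% to 69% favouring LED). Well above 5% is supported across these ranges. The absence of a deciding outcome and the day-3 mismatch rest on the text alone and need no assumption. An unseen document could resolve the missing designation, but the mismatch in the article would still need correcting.

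**What to change.** Before outcome data are examined by group:

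1. In section 3.13, name VAS pain at one assessed day, or one pre-specified VAS analysis over the assessed days, as the single primary outcome tested at 5%.
2. In section 2.3, reconcile the sample-size basis with that outcome. State the assumed difference, the SD, and the resulting power at the planned 38.
3. Label NRS-101, the other days, edema, trismus, temperature, dysphagia, hematoma, OHIP-14 and BAI as secondary. Report them with estimates and 95% confidence intervals, not as stand-alone proof of efficacy.
4. If the registry record or full protocol already names a primary outcome, align the article with it instead of choosing anew.

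Steps 1 and 3 cost only wording. Step 2 needs variability data for an assessed day, which the article does not give, and the restated power may be less favourable than 80%. The other cost is that a lone significant secondary result can no longer be claimed as efficacy.

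Correcting across all outcomes instead would be expensive. At the implied standardised difference of 0.99, Bonferroni over 13 tests (0.05/13 = 0.0038) leaves about 43% power at 17 per group. Over 46 tests (0.05/46 = 0.0011) it leaves about 27%. A single primary outcome keeps the efficacy claim at 5% without added participants, provided the sizing assumptions hold for the chosen day.

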## Discussion

4

The removal of retained third molars is a very common procedure that causes pain, edema, and trismus due to surgical trauma. Although the use of low-power laser in the postoperative has shown excellent results in the control of postoperative sequelae,^[12–14]^ this is the first study on the efficacy of the use of LED in this situation. Besides this, recently it was suggested that the accurate combination of irradiation site and PBM wavelength could optimize the postoperative results of this therapy after third molar removal surgeries. The best match would be the use of intraoral red light and extraoral infrared light.^[15]^ This study will evaluate whether the combination of 2 wavelength LEDs used intra and extraorally will bring benefits to the post-operative of third molar removal surgeries.

## Declarations

5

### Ethics committee

5.1

The study will be conducted in accordance with the guidelines of good clinical practice and has been approved by the Research Ethics Committee of UFRGS under process number 82570818.0.0000.5347. It follows the 466/2012 resolution of the National Health Council. After clarification and authorization of participants (or their guardians, for those under age) they shall sign a Free and Informed Consent Form. The identity of all individuals will be preserved in all stages of the research. Changes in the study will be reported to the committee. This will guarantee the confidentiality of each patient's data. The individual who does not attend the scheduled session will be excluded from the study.

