### Procedures to guarantee double blinding in the postoperative period

3.4

After the suture is completed, the researcher responsible for applying the LED will open the envelope containing the information from the experimental group in which the patient will be inserted and proceed to the experiment. A single examiner will run the LED application and will not perform any type of evaluation. Surgical procedures will be performed by the same surgeon. The preoperative and postoperative evaluations (1, 2, 5, and 7 days postoperatively) will be done by an examiner who will not be aware of the group in which each patient is allocated. The information that will be obtained in the evaluations will be written in the evaluator's file. Participants will not be aware of whether or not they received LED irradiation because the person responsible for applying the LED will position the insert in the irradiation sites in all participants and will only trigger light when and where predicted in the specific experimental group. The characteristic sound of the device will be triggered by recording in the control group.

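### Excluding randomised participants who miss a session breaks the comparison as randomised; the risk is selection bias first and power second

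*Protocol article*

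**What the plan says.** **The rule.** Section 5.1 (Ethics committee): "The individual who does not attend the scheduled session will be excluded from the study". It tolerates no missed session, is not limited to visits before randomisation, and does not say whether data already collected stay in the analysis.

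**Timing of allocation.** Section 3.4 (Procedures to guarantee double blinding): "After the suture is completed, the researcher responsible for applying the LED will open the envelope". The abstract and section 2.4 (Recruitment and randomization) agree. LED applications follow immediately after surgery and on days 1 and 2 (section 2.4). Assessments follow on days 1, 2, 5 and 7 (section 3.4). All return visits therefore come after allocation.

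**A second exclusion after allocation.** Section 5.3 (Discontinuing intervention) excludes from the study participants who report increased pain or show infection during treatment, with continued follow-up by the surgical team.

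**Loss allowance.** Section 2.3 (Sample calculation): "a minimum sample size of 17 cases per group was obtained, making a total of 34 participants for the study". The allowance is introduced thus: "Considering a loss of 10%, based on the study that was used for the sample calculation". The article converts it into two expected losses in each arm, which gives 19 per arm and 38 in total.

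**Analysis.** Section 3.13 (Statistical analysis) names no population that would bring excluded participants back.

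**The concern.** Randomisation makes the two arms comparable at the moment the envelope is opened. A rule that then drops people for not attending conditions the comparison on something that happens after allocation. A participant may stay away because pain, swelling or limited mouth opening is bad, or because recovery has gone so well that another visit seems pointless. If LED treatment affects those outcomes, it can also affect who attends, and it can do so with blinding fully intact. What remains is a comparison of attenders, and the direction of any distortion cannot be predicted. The exclusion in section 5.3 compounds this, because increased pain is itself a trigger in a trial of pain control.

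A smaller matter is that every such exclusion draws on a reserve of only 2 participants per arm.

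**Working it through.** **1. When the rule acts.** Allocation is revealed after suturing. The next attendances are day 1 and day 2 (LED and assessment) and days 5 and 7 (assessment only). A missed return visit can only occur after allocation, so this is a post-randomisation exclusion under any reading of the word session.

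**2. What exclusion means.** Section 5.1 does not say. Elsewhere the article ties exclusion to the analysis. Section 2.3 keeps the data of participants with surgical complications out of the statistical analysis. Section 3.2 (Surgery) describes data left out of the analysis and then calls this an exclusion. Removal from the analysis is therefore the likely meaning in section 5.1, but it is an inference.

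**3. The plan's own figure.** 17/(1 − 0.10) = 18.9, rounded up to 19 per arm, or 38 in total. This reproduces the stated size. The reserve is 19 − 17 = 2 per arm, or 2/19 = 10.5%.

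**4. Chance that the reserve is exceeded.** Let e be the total exclusion rate, with independent exclusions, so that losses per arm are Bin(19, e). The reserve fails in an arm at 3 or more losses. The chance that at least one arm falls below 17 is 1 − [P(Bin(19, e) ≤ 2)]².

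At e = 0.10, P(≤ 2) = 0.9^19 + 19(0.1)(0.9^18) + 171(0.01)(0.9^17) = 0.135 + 0.285 + 0.285 = 0.705, and 1 − 0.705² = 0.50.

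| Total exclusion rate | Expected loss per arm | 3 or more lost, given arm | At least one arm below 17 |
|---|---|---|---|
| 5% (assumed) | 0.95 | 7% | 13% |
| 10% (article) | 1.9 | 29% | 50% |
| 15% (assumed) | 2.85 | 56% | 81% |
| 20% (assumed) | 3.8 | 76% | 94% |

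**5. Power.** Inputs from section 2.3: "Using a power of 80% and level of significance of 5%, a minimum sample size of 17 cases per group was obtained", for day 3 VAS pain. No difference or SD is given, so the effect must be back-solved, assuming a two-sided two-sample test. The normal formula gives d = (1.960 + 0.842)·√(2/17) = 0.961. The noncentral t gives d = 0.991. With d = 0.991 and the t test at the expected arm size:

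| Total exclusion rate | Expected n per arm | Power |
|---|---|---|
| 0% | 19 | 84% |
| 10% | 19 × 0.90 = 17.1 | 80% |
| 15% | 19 × 0.85 = 16.15 | 78% |
| 20% | 19 × 0.80 = 15.2 | 75% |

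Each further participant lost per arm below 17 costs about 3 points at first (16 per arm 77.4%, 15 per arm 74.5%).

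**6. Dependence on the meaning of session.** Per-visit miss rates are assumed, with visits independent. If all four return visits count, 1 − (1 − 0.026)⁴ = 10.0%, so about 2.6% missed per visit already uses the allowance. At 5% per visit, 1 − 0.95⁴ = 18.5% are excluded, and the chance that at least one arm falls below 17 is 92%. If only the two return LED visits count, 5% per visit gives 1 − 0.95² = 9.8% and a chance of 48%.

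**The case against.** The strongest reply is that a 10% allowance exists precisely to absorb non-attendance, that power at 10% loss is still 80%, and that a 50% chance of one arm falling below 17 applies to any trial with 19 per arm and 10% expected loss. All of this stands. It means the power figures do not by themselves condemn the rule. Losses may or may not exceed 10%. The source of that figure is not at hand, so it cannot be said that this trial's exclusions come on top of it. The reply does not touch the bias argument, which needs no power figure.

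A second reply is that analysis populations and missing-data methods are commonly left to an analysis plan or full protocol that is not shown. That is fair as to methods. But section 5.1 does not leave the matter open: it states an exclusion, and that statement needs correcting.

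A reader might infer three stronger points that the article does not support:

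- **A missed day 7 visit discards the day 1 and day 2 data.** The word session is used only in section 5.1 and is undefined. If it means LED sessions, a missed day 7 triggers nothing. Nor does section 5.1 itself mention deleting data.
- **The surgical-complication exclusion may follow allocation.** Its triggers arise during surgery, and section 3.3 stops the duration clock at the end of the suture. The envelope is opened only afterwards, by the researcher who applies the LED and not by the surgeon. The facts precede allocation.
- **Analgesic use is a further established exclusion.** The sentence in section 3.2 about leaving data out does not make clear which participants it means.

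**Conclusion.** The concern holds as a matter of bias. As written, section 5.1 removes randomised participants for non-attendance, a factor plausibly linked to the outcomes, and nothing in the article restores them. The size and direction of the bias cannot be estimated from the document. That excluded participants leave the analysis is the likely reading, not a stated one.

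The cost in power is secondary and modest. At the article's own 10% loss the reserve is almost spent on average (1.9 of 2), with about an even chance that one arm falls below 17, yet power is about 80%. The fall to 78% or 75% rests on assumed exclusion rates of 15% and 20%, independent exclusions, and an effect of about 0.99 SD that is back-solved from the sample size and is not a planned effect stated in the article.

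**What to change.** **Replace the sentence in section 5.1** with wording to this effect: participants who miss an LED session or an assessment remain in the study, are invited to all later assessments, and are analysed in their allocated arm with all observed data. Missed LED sessions are recorded as non-adherence and missed assessments are treated as missing data.

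**Analysis.** For VAS and NRS-101 pain, facial measures and mouth opening, a likelihood-based repeated-measures model over days 1, 2, 5 and 7 is one suitable choice, since it does not need complete cases. It does not suit every outcome: OHIP-14 and BAI have a single postoperative measurement, and dysphagia and hematoma are ordinal, so these need their own methods under the same as-allocated principle. Report adherence to the three LED sessions by arm, and give an attenders-only analysis as sensitivity.

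**Reconcile section 5.3** with this wording as regards the analysis only. Its clinical management is not in question.

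**Cost.** A change of protocol wording, reported to the ethics committee as section 5.1 already provides, and a model available in SAS, the software named in section 3.13. No extra participants or visits are needed. If all 19 per arm are kept and analysed, power for the back-solved effect is about 84%.
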